### Data analysis

The data will be exported from Unipark and analysed with SPSS version 21.0 (IBM Corp., Armonk, NY) and Mplus version 7.0 (Muthén & Muthén, Los Angeles, CA). Data cleaning and analyses will be performed using SPSS and Mplus syntax operations. We will conduct descriptive analyses to describe the study population. Possible baseline differences between trial arms will be statistically tested. We will adjust further analyses for imbalances in the baseline scores.

The primary analysis will be by intention to treat. As sensitivity analyses, only completers of all assessments will be analysed. The impact of the DA on the primary outcome will be analysed using *χ*^2^-tests. The numeric secondary outcomes will be analysed using analyses of variance; categorical secondary outcomes will be analysed using *χ*^2^-tests. Additionally, latent change model analyses will be performed for continuous longitudinal outcome data. Latent transition analyses will be performed for categorical longitudinal outcome data. To handle missing data, full information maximum likelihood estimation will be conducted in MPlus. To investigate the mediation and moderation effects of the secondary and demographic variables, mediation and moderation analyses will be performed using the PROCESS macro version 2.13 (Andrew F. Hayes, http://www.processmacro.org). in SPSS. As part of the questionnaire adaptation, factor, reliability, and correlation analyses will be performed.

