### Decision aid

The DA was developed and piloted as part of this study. The DA and questionnaires for evaluation were programmed in Unipark, an online survey tool (QuestBack GmbH, Cologne, Germany). The structure of the DA was based on that of Mathieu et al. [19]. The DA was conceptualized as an interactive online tool consisting of a static information part and an interactive part.

We conducted a pilot study in March 2014, which showed that our study methods were feasible and acceptable to women aged 50. This quantitative pilot, to which 300 women were invited of which 53 participated, also showed that women accessed the DA and worked through it and that the questionnaires were accessed and answered. The pilot indicated that about a third of women dropped-out of the study prematurely. In a preceding qualitative pre-test both DA and questionnaires were evaluated with women of the target group through think-aloud protocols. The DA was additionally qualitatively piloted with experts from the National Network Women and Health.

In line with IPDAS criteria [25], the DA presents the options of choice (participation or non-participation in the MSP) in a decision-relevant context. The advantages and disadvantages of the MSP and their probabilities are described. These include the probabilities of a positive and negative screening result in absolute numbers supported by graphic presentations to allow women to form a realistic expectation regarding the initial outcome of the screening. We explain overdiagnosis, overtreatment, and the procedure following a positive result. Positive and negative information are presented in a balanced way according to current evidence. Step-by-step navigation through the websites of the interactive online DA facilitates a structured progress. Participants receive tailored feedback based on previous entries directly before making the decision. The studies from which the data for the DA originate are cited and provide the participants with easy access to the original sources via links.

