### Sample size

Sample size was calculated using G* Power for the primary outcome (informed choice). Based on the study of Mathieu et al. [19], we determined a difference in the proportion of informed choices of 7 percentage points as the minimum clinically important difference for the power calculation. A sample size of 740 women (370 per arm based on a 1:1 allocation ratio) will enable the detection of a between-group difference of 7 percentage points given 80 % power and a 5 % (one-tailed) significance level. Allowing for an estimated response rate of 15 % and early drop-out of one-third of initial participants, we aim to invite 7400 women to take part in the study.

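### The primary analysis is labelled intention to treat, but its chi-square test counts only women with an observed outcome, and the completers-only sensitivity analysis cannot detect bias from attrition that differs by arm

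*Protocol article*

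**What the plan says.** All references are to the protocol article.

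- **Data analysis, population.** "The primary analysis will be by intention to treat. As sensitivity analyses, only completers of all assessments will be analysed". No other sensitivity analysis is named.
- **Data analysis, test.** "The impact of the DA on the primary outcome will be analysed using" chi-square tests.
- **Data analysis, missing data.** After the sentences on latent change and latent transition models: "To handle missing data, full information maximum likelihood estimation will be conducted in MPlus". The analyses it serves are not listed.
- **Sample size.** The target is 740 women, 370 per arm, to detect a 7-point difference. The number to invite allows for a 15 % response and "early drop-out of one-third of initial participants".
- **Decision aid, pilot.** "The pilot indicated that about a third of women dropped-out of the study prematurely". No split by arm is given.
- **Consent and data collection.** Random assignment is described together with the T2 mailing, two weeks after the T1 email. One arm receives a link to the decision aid (DA) and the T2 questionnaire; the other receives the questionnaire only. Reminders at every wave go to all women who initially agreed.
- **Table 1.** Uptake is collected only at T3; intention is collected only at T1 and T2.

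**The concern.** The label, the test and the sensitivity analysis do not fit together. An intention-to-treat comparison concerns all randomised women in their assigned arms. A chi-square test on a two-by-two table has no place for a woman without an outcome, and the plan gives no rule that would assign her one. The result is valid for all randomised women only if missing outcomes do not distort the arm difference. The one planned sensitivity analysis also conditions on observed outcomes, so agreement between the two would be no reassurance.

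This matters because the arms are asked to do different things. Only one is also asked to use the DA, and the trial is unblinded. If less engaged or less knowledgeable women leave that arm more often, those who stay look better informed even if the DA does nothing. The primary claim of effectiveness is at stake.

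**Working it through.** **1. The plan's own figure.** 7400 × 0.15 = 1110 initial participants; 1110 × 2/3 = 740. The chain reproduces exactly. The trial is therefore powered on the women who remain, which fits a test on observed outcomes.

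**2. How much could be missing.** The one-third is a share of initial participants, and assignment is described with the T2 mailing, so some loss may come first.

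| Share of the 370 lost after randomisation | Randomised | Missing | Missing, % of randomised |
|---|---|---|---|
| all | 1110 | 370 | 33 % |
| half | 925 | 185 | 20 % |
| none | 740 | 0 | 0 % |

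One-third is the maximum under the plan's own drop-out figure.

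**3. Does FIML reach the primary test?** FIML is an estimation method for a model; a chi-square test on a table does not use it. Even a model with arm and one binary outcome, fitted by FIML without auxiliary variables, returns the observed proportions. It adds information only when other variables, such as T1 or T2 measures, are in the model.

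**4. How different is the sensitivity set?** Completers answered T1, T2 and T3. If implementation is measured by uptake, a woman needs T3 to have a primary outcome. The two sets then differ mainly by women who answered T3 but missed an earlier wave. Both exclude every woman without an outcome.

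**5. Illustrative size under no true effect.** The inputs are assumptions, not figures from the article: control retention 2/3 (all loss after randomisation); extra loss *e* in the DA arm of 0.05 to 0.15; extra leavers' informed-choice rate lower by *g* = 0.20 to 0.30 than that of the women retained in the DA arm.

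Let *r* be the rate among retained control women and *d* the rate among retained DA women. With no effect, the two-thirds of the DA arm who would have stayed at control retention also have rate *r*:

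(2/3)·r = (2/3 − e)·d + e·(d − g), so d − r = e·g/(2/3) = 1.5·e·g.

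The base rate cancels, so no control rate is needed.

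| e | g | Spurious difference |
|---|---|---|
| 0.05 | 0.20 | 1.5 × 0.010 = +1.5 points |
| 0.10 | 0.20 | 1.5 × 0.020 = +3.0 points |
| 0.10 | 0.30 | 1.5 × 0.030 = +4.5 points |
| 0.15 | 0.30 | 1.5 × 0.045 = +6.75 points |

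With 80 % retention in control (the 20 % row in step 2), the divisor is 0.80 and the range is 0.010/0.80 = 1.25 to 0.045/0.80 = 5.6 points.

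**6. What analyses based on counts would show.** Take an observed difference of +7 points with one-third missing in each arm.

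- Missing counted as not informed: 7 × 2/3 = 4.7 points.
- Extreme cases: 4.67 − 33.33 = −28.7 and 4.67 + 33.33 = +38.0 points.
- Tipping point: the overall difference is 4.67 + (1/3) × (missing DA rate − missing control rate). The point estimate reaches zero when missing DA women are 4.67 × 3 = 14 points below missing control women.

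**The case against.** The best defence is that this is a condensed article. It commits to intention to treat, does not confine the FIML sentence to particular analyses, and plans latent transition models for categorical data that could use T1 and T2 information. An analysis plan not shown may say how missing outcomes enter the primary test. That stands as far as detail is concerned. It does not settle the point, because the article itself fixes the test and the sensitivity analysis, and neither serves the stated label.

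Several stronger readings are tempting, and the article does not support them:

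- *That the plan says it discards one-third of randomised women.* It does not say so. Exclusion follows from the choice of test, and one-third is an upper limit.
- *That the completers analysis simply repeats the primary one.* A woman who missed T2 but answered T3 may be in one and not the other. The size of the overlap is not given.
- *That women must work through the DA to reach the T2 questionnaire.* Only a link to both is described. Extra burden in that arm is plausible, but no figure for attrition by arm is reported.
- *That the bias would exceed the 7-point target.* Measuring the leavers' gap against the rate before the extra loss gives e·g/(2/3 − e), up to 0.045/0.5167 = 8.7 points. In that case the leavers lie 30 + 8.7 = 38.7 points below the retained DA women, outside the assumed 20 to 30.

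It is also fair that attrition need not be completely random within arm. Selection that shifts both arms equally leaves the difference unbiased. The concern is attrition that differs by arm.

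**Conclusion.** The point holds in this limited form. As written, the primary test is an observed-case comparison under an intention-to-treat label, and its only sensitivity analysis cannot test the assumption on which it rests. Between 0 % and 33 % of randomised women could lack the outcome. Under the stated assumptions, attrition that differs by arm could by itself produce about +1.5 to +6.8 points, from a fifth of the target effect to nearly all of it. These figures show what is possible and do not predict what will happen: the excess loss and the gap are assumed, and the range narrows if part of the drop-out precedes randomisation. This goes beyond missing detail, because the sensitivity analysis that is named is unsuited to its purpose and can be supplemented cheaply.

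**What to change.** 1. State how randomised women without an informed-choice outcome enter the primary analysis. Keep them in through a categorical-outcome model with FIML and auxiliary variables, or through multiple imputation by arm from T1 and T2 data (for example knowledge, attitude, intention, decision stage, education and eHealth literacy). Report the risk difference.
2. First confirm that arm can be attached to the records. Ethical approval describes linking the waves only by a self-generated code, so a woman who answered T1 and nothing later may have no arm on her research record.
3. Keep the completers analysis, and add two that need only the observed counts and the number randomised per arm: missing counted as not informed, and a tipping-point analysis that varies the assumed rate among missing women separately by arm.

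The cost is a few sentences and modest programming; the T1 and T2 variables are already collected. Counting missing as not informed shrinks the difference (7 points becomes about 4.7 with one-third missing in each arm), so it belongs among the sensitivity analyses and should not be the primary one.

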In summary, this will be the first study to assess the impact of an online DA for the German MSP in a randomized controlled trial. The results of this research will be important for the following reasons: (1) they will provide information on the level of informed choice under usual care; (2) they will show whether a DA is helpful in increasing informed choice; and (3) they will indicate whether a DA is acceptable to women. The DA developed in this project will provide a support tool for decision making that can be used in further studies on informed choice and evaluated in other populations. If the DA proves to be effective in increasing the proportion of informed deciders, our results will be relevant to practice. Hence, the DA could be used on a large scale.

## Abbreviations

MSP: Mammography screening programme
DA: Decision aid
InEMa: Informed Choice of German and Turkish Women for Participation in the MSP (study title)
IPDAS: International Patient Decision Aids Standards
